**Methods and analysis:**

The research will use a before-and-after quasi-experimental study design to measure the effects of the reform on service readiness and service utilisation and a cross-sectional qualitative study to explore the implementation experience, political economy and gendered effects of these reforms. Data to measure the effects of autonomy will be collected from a sample of 80 health facilities and 1600 clients per study arm. Qualitative interviews will involve approximately 83 facility managers and policymakers at the county level, distributed across intervening (36) and planning to intervene (36) counties. Additionally, 11 interviews will be conducted at the national level with representatives from the Ministry of Health, the National Treasury, the Controller of Budget, the Council of Governors, the Auditor General and development partners. Given the uncertainty surrounding the implementation of the reforms, this study proposes two secondary designs in the event our primary design is not feasible—a cross-sectional study and a quasi-experimental interrupted time series design. The study will use a difference-in-difference analysis for the quantitative component to evaluate the effects of the reforms, while using thematic analysis for the qualitative component to evaluate the political economy and the implementation experience of the reforms.

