### Evaluating the effects of autonomy reforms

#### Primary study design

We will employ a before and after quasi-experimental study to measure the effects of health facility autonomy on health facility readiness, functionality, service utilisation and client satisfaction of health facility autonomy reforms. We will conduct an assessment before implementation of the FIF reforms and an assessment after 12 months of implementation of the FIF reforms. The primary outcome of interest will be health facility readiness.

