#### Sample size and sampling

There will be three levels of sampling for this study. The first level is county sampling, where we will purposively sample four counties already implementing autonomy reforms, four planning to implement the intervention and four not implementing as control. From the sampled counties, we will randomly sample 80 health facilities per group, assuming a mean difference of 10% in facility readiness between the two groups and a population variance of 400 across the groups using 80% power, 95% confidence level and a design effect of 1.2. Because the autonomy reforms have the biggest effects on facilities that raise revenue, we will sample all facilities from levels 4–6 from the selected counties. Leve 4-6 facilities are allowed by law to charge user fees. For the remaining facilities, we will then randomly sample levels 2 and 3. The numbers will be proportionate, targeting a maximum 20 facilities per county. For clients, we will randomly sample a minimum of 1600 clients exiting the health facilities per group, assuming a mean difference of 10% in client satisfaction between the two groups and a population variance of 55 across the groups using 80% power, 95% confidence level and a design effect of 3. To calculate the variance, we took an average of the outcome of the interest in the control and intervention (expected).^28^,^30^ We divide the 1600 clients equally among the selected facilities to achieve a minimum sample of 20 per facility as is recommended for cluster randomised trials.^28 30^ The following sample size calculation formula was used:

,$$n=\left(Z_{\alpha /2}+Z_{\beta \;}\right)sqrd\times 2\times \;\sigma^{2}\;/d^{2}$$

where Z_α/2_=1.96 (5% significance), Z_β_=0.84 (80% power), σ^2^=population variance of 59 (SD of 19 per group) and d=mean difference of 8% between the two groups.

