#### Data analysis

We will compute means, medians and SD of all study variables and key sample characteristics at the baseline and end line. To determine the effects of autonomy reforms on service utilisation and client satisfaction, we will use the quasi-experimental difference-in-difference (DiD) analysis. We will first compute the differences in means between the baseline and end line for each study group, then the differences in mean between the intervention and control.

Thereafter, we will estimate the effect using multivariate regression analysis. This means that we will calculate the DiD while controlling for other covariates that are likely to affect outcomes such as facility average insurance coverage, average distance to facility for facility catchment population, health worker density and facility size. The unit of analysis will be the health facility, and the outcomes of interest will be service utilisation and client satisfaction.

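### The analysis section confines the difference-in-differences estimate to service utilisation and client satisfaction, leaving out facility readiness, the declared primary outcome

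*Protocol article*

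**What the plan says.** The Primary study design section states: "The primary outcome of interest will be health facility readiness". It describes the before-and-after design as one "to measure the effects of health facility autonomy on health facility readiness, functionality, service utilisation and client satisfaction". The quantitative Sample size and sampling section sets 80 facilities per group, "assuming a mean difference of 10% in facility readiness between the two groups", with a variance of 400, 80% power, 95% confidence and a design effect of 1.2.

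The quantitative Data analysis section starts with description: "We will compute means, medians and SD of all study variables and key sample characteristics at the baseline and end line". It then assigns the effect analysis: "To determine the effects of autonomy reforms on service utilisation and client satisfaction, we will use the quasi-experimental difference-in-difference (DiD) analysis". After listing the covariates for the regression version, it closes: "The unit of analysis will be the health facility, and the outcomes of interest will be service utilisation and client satisfaction".

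The abstract's Methods and analysis paragraph says the design is meant "to measure the effects of the reform on service readiness and service utilisation", and adds: "The study will use a difference-in-difference analysis for the quantitative component to evaluate the effects of the reforms".

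**The concern.** The analysis section specifies the effect analysis in some detail: the method, the covariates, the unit of analysis and the outcomes. The outcomes it names, in two separate sentences, exclude the one the article calls primary. An analyst working from this section would produce adjusted effect estimates for utilisation and satisfaction and only a descriptive table for readiness.

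At stake is which result carries the conclusion on whether autonomy works. The study is non-randomised, its 12 counties are chosen purposively, and it announces two fallback designs. In that setting a clearly fixed primary analysis is one of the main protections against selective emphasis. At present one section fixes the primary outcome and another describes an effect analysis that does not contain it.

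**Working it through.** **1. The outcome lists side by side**

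| Place in the protocol article | Outcomes named | Role |
|---|---|---|
| Abstract, Methods and analysis | readiness, utilisation | effects to be measured |
| Primary study design | readiness, functionality, utilisation, satisfaction | effects to be measured; readiness primary |
| Sample size and sampling (quantitative) | readiness (80 facilities per group); satisfaction (1600 clients per group) | basis of sample size |
| Data analysis, sentence introducing DiD | utilisation, satisfaction | DiD outcomes |
| Data analysis, closing sentence | utilisation, satisfaction | outcomes of interest, facility as unit |

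Readiness is in every row except the two that define the effect analysis. Within the Data analysis section, only the descriptive summaries of all study variables would cover it. The Secondary study design section does not assign a readiness analysis either: the cross-sectional fallback names no outcome, and the interrupted time series uses routine performance indicators.

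**2. The facility sample size, reproduced**

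Inputs from Sample size and sampling: d = 10, variance 400 (SD 20), z values 1.96 and 0.84, design effect 1.2. The 10% is read as 10 points on the scale that has this variance.

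- n = (1.96 + 0.84)² × 2 × 400 / 10² = 7.84 × 8 = 62.72
- 62.72 × 1.2 = 75.3, so 76 per group
- Stated: 80, which is 4 more and on the conservative side. It fits rounding 19 per county up to 20 in four counties.
- Effective size at 80 per group: 80 / 1.2 = 66.7. Standard error: 20 × √(2/66.7) = 3.46. Power: Φ(10/3.46 − 1.96) = Φ(0.93) ≈ 82%.

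The facility sample therefore does rest on readiness. The formula compares two means at a single time, however; it is not a DiD calculation. The legend under the printed formula gives other values (variance 59, difference 8%). That is a separate matter, and they are not used here.

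**3. Power if readiness is analysed by DiD**

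Assume equal variance at both rounds, the same design effect on the change, and no gain from covariates. With baseline-to-endline correlation ρ, the SD of the change is 20 × √(2(1 − ρ)). The document does not give ρ, so a range is shown.

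| Assumed ρ | SD of change | Facilities needed per group for 80% power | Power at 80 per group |
|---|---|---|---|
| 0 | 28.3 | 151 | 53% |
| 0.3 | 23.7 | 106 | 68% |
| 0.5 | 20.0 | 76 | 82% |
| 0.7 | 15.5 | 46 | 96% |

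At ρ = 0.5 the change has the same SD as a single measurement, so the DiD needs the same 76 per group as step 2. Below that it needs more.

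**The case against.** The best defence is that the article read as a whole points to readiness. The abstract pairs readiness with a general statement that DiD serves the quantitative component. The Primary study design section lists readiness among the effects to be measured, and the Data collection section says the facility questionnaire will evaluate the impact on equipment, medicines and service availability. On that reading the Data analysis section contains a slip. This is probably right about the cause. It does not remove the conflict, because the abstract ties DiD to no named outcome and the specific section twice names others.

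A second defence is that a journal article condenses a fuller protocol and that a separate analysis plan may exist. That would answer a complaint about missing detail. Here the detail is given, and it contradicts the declared primary outcome.

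Three stronger readings are tempting and should not be drawn:

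- A reader might infer that the study never estimates its primary effect. The documents support this only for the Data analysis section taken literally; the abstract's general DiD statement points the other way.
- A reader might infer that utilisation and satisfaction have become co-primary, with an inflated false-positive rate. The article declares a single primary outcome and nowhere makes these two co-primary. Nor is it a fault that utilisation has no sample size of its own, since non-primary outcomes often have none.
- A reader might infer that everything the study was sized for is left unanalysed. This applies to the 80 facilities. The 1600 clients per group were sized on satisfaction, which is in the DiD.

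**Conclusion.** The point holds as a contradiction in the current text. The outcome list in the Data analysis section conflicts with the primary outcome declared under Primary study design, with the basis of the facility sample size, and with the abstract. Taken literally, that section leaves the primary outcome with descriptive summaries and no effect estimate. This conclusion rests on the wording alone and on no numerical assumption.

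The power figures are a caveat to the remedy and not the defect itself. The 80 facilities give about 82% power for a single-time comparison of readiness. For a DiD they give between 53% and 96% over assumed correlations of 0 to 0.7, and reach the 80% target at a correlation of about 0.5 or higher. These figures depend on the assumptions stated in the working.

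Although the cause is probably a drafting slip, it concerns the primary outcome and should be settled before endline data are analysed.

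**What to change.** Amend the Data analysis section along these lines: *The primary analysis is the difference-in-differences estimate for health facility readiness (intervention minus control, endline minus baseline), with the facility as the unit of analysis. Service utilisation and client satisfaction are secondary outcomes, analysed with the same model. The conclusion on effectiveness rests on readiness.* Functionality, also listed under Primary study design and absent from the analysis section, should be placed among the secondary outcomes or removed.

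The amendment should point to where the readiness measure is defined. The article text lists its likely components and refers to a supplemental table that is not shown here. Add a sentence saying that the 80% power was calculated for a single-time comparison, and state the baseline-to-endline correlation assumed for the DiD, or a range with the resulting power.

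The cost is a few sentences. No new data collection is needed: the facility questionnaire already covers services, medicines, laboratory services and equipment, and is administered before roll-out and 12 months after. If a plausible correlation turns out to be well below 0.5, the authors would have to report lower power for the primary analysis or reconsider the number of facilities.

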### Autonomy reforms in Kenya

Kenya has been on a path to improve service delivery through devolution and more recently increased investments in PHC services.^14^ Kenya devolved health service delivery to county governments in 2013. Health facilities enjoyed some level of autonomy before devolution (health facility administration, financial management, procurement, human resource management and strategic management), through the health management services fund for hospitals and health sector services fund for health centres and dispensaries, which was shown to be effective in enhancing service delivery.^13^ However, following the devolution of health services in 2013, health service delivery was reorganised with county health management teams (CHMTs) taking up the responsibility for the management of health services and usurping the autonomy of subcounty and facility management committees.^7^

Over time, various counties have acknowledged the need for facility managerial autonomy and have allowed facilities some level of financial and procurement autonomy.^15^ Across these counties, this has been done through various means including enactment of county-level legislation and/or adoption of county-level policies to facilitate health facility autonomy. However, many counties have continued to limit the autonomy of health facilities. At the time of writing this protocol, the country had recently enacted a new Facility Improvement Funds (FIF) law that aimed at according some level of financial and procurement autonomy to public sector health facilities across the country.^16^ The law requires that facilities in the country are allowed to retain and spend their own source revenue. This law mandates all counties to implement autonomy reforms. However, the government was yet to establish guidelines for the implementation of this new law. Furthermore, due to the devolution of the management of health services in the country, the adoption and implementation of this new law is likely to depend on individual county leadership, unlike before the devolution when national laws were adopted exactly as guided by the national government. This will likely lead to variations in uptake of facility autonomy across counties in terms of both time of implementation and mechanism of implementation. These variations in implementation provides an opportunity to evaluate the effectiveness and implementation experience of autonomy reforms.

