#### Study population

We intend to assess selected counties, selected facilities and clients receiving services from the selected facilities. For the county assessment, the study population will be the 47 counties from which we have selected 12 counties—4 implementing autonomy reforms, 4 planning to implement and 4 controls. For the facility assessment, the study population will be all county-owned public facilities within the selected counties across all level 2-6 of service provision level 2 (dispensaries), level 3 (health centers) level 4, 5 and 6 (hospitals) (table 1). Level 1 in Kenya comprises community health services, these will be excluded as at the time of the protocol, there were minimal to no mechanisms for payment for services provided at that level. For the client exit interviews, the study population will be all patients or carers whose patients had received services from the selected facilities on the day and time of the survey. These will include patients or carers seeking services such as outpatient services, antenatal services, postnatal services, child welfare services, management of chronic illness and maternity services and those discharged from inpatient care.

**Table 1 T1:** Selected counties with distribution of facilities

Group	County	Level 2	Level 3	Level 4	Level 5	Level 6	Total facilities in county
Controls	Tana River	44	5	3	0	0	52
	Migori	115	19	14	0	0	148
	Embu	88	9	4	1	0	102
	Kirinyaga	47	22	4	0	0	73
Already implementing	Makueni	189	39	12	0	0	240
	Mombasa	40	8	4	1	0	53
	Nakuru	140	26	17	1	0	184
	Kajiado	81	21	5	0	0	107
Intervention	Kakamega	111	48	12	1	0	172
	Lamu	29	3	3	0	0	35
	Homabay	120	48	16	0	0	184
	Nyandarua	54	24	2	0	0	80
	Total by level	1058	272	96	4	0	1430

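### The reform is adopted by county (4 versus 4), but the facility is fixed as the unit of analysis with no county-level inference described, and the stated 80% power makes no allowance for having only eight counties

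*Protocol article*

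**What the plan says.** - **Level of adoption.** The section Autonomy reforms in Kenya says that "the adoption and implementation of this new law is likely to depend on individual county leadership", and expects counties to differ in when and how they implement.
- **Counties.** Under the quantitative Sample size and sampling heading, "we will purposively sample four counties already implementing autonomy reforms, four planning to implement the intervention and four not implementing as control". The Study population section gives the primary contrast as "4 planning to implement and 4 controls".
- **Facilities.** "we will randomly sample 80 health facilities per group", "targeting a maximum 20 facilities per county". The readiness calculation is made "assuming a mean difference of 10% in facility readiness between the two groups" with variance 400, "using 80% power, 95% confidence level and a design effect of 1.2". The formula printed in that section uses the normal quantiles 1.96 and 0.84.
- **Analysis.** The Data analysis section plans a covariate-adjusted difference-in-difference regression and states "The unit of analysis will be the health facility". The covariates are insurance coverage, distance to facility, health worker density and facility size. County does not appear. The outcomes named there are service utilisation and client satisfaction. Readiness is named as primary under Primary study design.

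**The concern.** Within the primary comparison, exposure varies only between eight counties. Facilities in one county share its budget, supply chain and management team, so a change that affects a whole county between the two rounds moves up to 20 sampled facilities together. Facility covariates do not remove that. If facilities are then analysed as separate observations, the interval around the reform effect is too narrow and chance county movements can pass as an effect.

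Planning has a related weakness. A design effect inflates the variance, but it does not account for estimating that variance from eight counties, which leaves 8 − 2 = 6 degrees of freedom. A power figure based on normal quantiles is then too favourable. At stake are the interval and significance of every difference-in-difference result, and the credibility of the stated power for the primary outcome.

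**Working it through.** **Inputs from the article (readiness):** difference d = 10, variance 400 (SD 20), two-sided 5%, 80% power, design effect (DE) 1.2, 80 facilities per group, 4 counties per group. Cluster size is taken as 80/4 = 20, the stated maximum. **Not given:** the county ICC and the before-after correlation r. Both are shown as ranges.

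**1. The plan's own figure.** n = (1.96 + 0.84)² × 2 × 400 / 10² = 62.7. Multiplying by 1.2 gives 75.3, so 76 per group. The article states 80, which equals 20 facilities × 4 counties and is slightly conservative. With 80 per group and DE 1.2, normal-theory power is 82.3%. On its own terms the calculation is adequate.

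**2. What DE 1.2 implies.** DE = 1 + (20 − 1) × ICC, so ICC = 0.2/19 = 0.0105.

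**3. A facility-level test with no county-level inference.** The true standard error is √DE times the one used, so true two-sided error = 2(1 − Φ(1.96/√DE)).

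**4. A county-level test under the single-time formula.** SE = √(2 × 400 × DE/80). Power comes from a noncentral t with 6 df, critical value 2.447 and noncentrality 10/SE.

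| ICC | DE | True error, step 3 | SE | Power, step 4 |
|---|---|---|---|---|
| 0 | 1.00 | 5.0% | 3.16 | 75% |
| 0.0105 (implied) | 1.20 | 7.4% | 3.46 | 67% |
| 0.05 (assumed) | 1.95 | 16% | 4.42 | 48% |
| 0.10 (assumed) | 2.90 | 25% | 5.39 | 35% |

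At DE 1.2 the difference detectable with 80% power is about 11.7 points. Under this formula 80% is not reached at any ICC of 0 or above.

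**5. The planned difference-in-difference.** With equal variance at both rounds, the variance of a facility's change is 2 × 400 × (1 − r), so SE = √(2 × 800 × (1 − r) × DE/80). The ICC and DE now refer to the changes. Power with 6 df:

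| r | DE 1.2 | DE 1.95 | DE 2.9 |
|---|---|---|---|
| 0 | 40% | 27% | 20% |
| 0.5 | 67% | 48% | 35% |
| 0.7 | 87% | 68% | 52% |

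At DE 1.2, power reaches 80% at r of about 0.63. The single-time result in step 4 equals the difference-in-difference result only at r = 0.5.

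**The case against.** The strongest reply is that the article never says facilities are treated as independent and does not say how standard errors are computed. A facility-level regression can carry county-clustered inference, and a condensed article may leave the variance estimator to a fuller plan. This stands in part. A reader might infer that the standard errors are certain to be too small; the text does not establish that, so the error rates above are conditional on the regression being run as worded. But the article does more than stay silent. It names a unit that is not the unit of adoption, and it publishes a power figure that ignores the number of counties. Conventional clustered standard errors are also unreliable with eight clusters, so the method needs naming.

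Other points that stand:
- Clustering is allowed for in planning, though thinly. It is not ignored.
- The 80% with DE 1.2 is for readiness, while the Data analysis section names utilisation and satisfaction. The error-rate and power results therefore do not describe one and the same analysis. Inflated error belongs to an unadjusted test, and reduced power to a valid county-level one.
- A reader might infer that the study simply has 67% power instead of 80%. For a difference-in-difference that needs r = 0.5, which the article does not give; a higher correlation could restore 80%.
- The design removes stable county differences, and shocks common to both arms cancel. Only the unknown ICC of the changes matters.
- The implied ICC assumes 20 facilities in every county, while the article gives 20 as a maximum.

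**Conclusion.** The point holds in this form. Adoption is by county, 4 versus 4 and purposive, yet the facility is the stated unit of analysis, with no county-level inference described. Without such inference, a nominal 5% test has a true error of about 7% at the protocol's own design effect, and 16% or 25% at assumed ICCs of 0.05 or 0.10.

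For readiness, the stated 80% is not supported as calculated: the protocol's single-time formula with 6 df gives about 67% at DE 1.2 and no more than 75%. Whether the difference-in-difference itself falls short cannot be settled from the article, because at DE 1.2 its power lies between 40% and 87% for r between 0 and 0.7. These figures assume 20 facilities per county and, for the difference-in-difference, equal variance at both rounds.

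**What to change.** Keep the facility-level data and the covariate-adjusted model, but state a few-cluster inference by county as primary for every difference-in-difference outcome, readiness included. Suitable choices are a t-test on the eight county mean changes (6 df) or a wild cluster bootstrap by county. Permutation over the C(8,4) = 70 possible splits can serve as a sensitivity analysis. Its smallest two-sided p-value is 2/70 = 0.029, so 5% is attainable, but counties were not randomised and it should not be the primary basis.

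Restate the readiness power with 6 df as a range over county ICC and before-after correlation, with the assumptions given, and not as a single 80% or 67%.

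The cost is a change of wording, wider intervals and a less favourable stated power; no new data are needed. Few-cluster inference does not remove bias from shocks specific to one arm, and the text should say so.
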